### Prospective visit calendar

Participation to the study will be proposed during hospitalization after delivery. The follow-up of the cases and the control will be similar. The total duration of participation of each dyad is 20 months. The design of the study will not change the eventual care provided to the dyad. If some care is proposed or given, a description of this care will be included in the data collection.

The study’s follow-up includes 6 visits (Table 1).

**Table 1 Tab1:** Visits description and data collected

Timepoint	1st visit Inclusion	2nd visit	3rd visit	4th visit	5th visit	6th visit Thanks & Survey
	Maternity	Obstetrical Consultation	Home	Home	Psychological Laboratory	Home
	S 1	S 6–8	M 6	M 12	M 18	M20
ENROLMENT	X					
- Inclusion criteria	X					
- Non-Inclusion criteria	X					
- Informed consent	X					
ASSESSMENTS	X					
- Demographic information	X					
- Social information	X					
- Medical information	x					
- MINI^a^ (mother)	X					
- BDI^b^ (mother)	X			X		
- STAI^c^ (mother)	X			X		
- PSSQ^d^ (mother)	X			X		
- EPDS^e^ (mother)		X				
- AAN^f^ (mother)		X				
- DSST^g^ (infant)			X	X	X	
- CIB^h^ (dyad)			X	X		
- QT6^i^ (mother)			X			
- ADBB^j^ scale (infant)			X	X		
- IPDE^k^ (mother)			X			
- SSP^l^ (infant)					X	

^a^MINI: Mini International Neuropsychiatric Interview

^b^BDI: Beck Depression Inventory

^c^STAI: Scale Trait Anxiety Inventory

^d^PSSQ: Perceived Social Support Questionnaire

^e^EPDS: Edinburgh Postnatal Depression Scale

^f^AAN: Adult Attachment Narratives

^g^DSST: Denver Developmental Screening Test

^h^CIB: Coding Interactive Behaviour

^i^QT6: Questionnaire on the 6 months old infant’s Temperament

^j^ADDB scale: Alarm Distress BaBy scale

^k^IPDE: International Personality Disorders Examination

^l^SSP: Strange Situation Procedure

During the first visit (during the week after delivery), informed consent, data (demographics, age, marital status, level of education, financial resources, socio-economic data of the child’s father, developmental data of the child’s siblings) will be collected. Additionally, medical information, including gestation and parity, pregnancy records, and medical, surgical and psychiatric history, will be extracted from the mother’s charts. Direct assessment of perceived social support with the Perceived Social Support Questionnaire (PSSQ) [24] and psychiatric condition will be provided with the Mini International Neuropsychiatric Interview (MINI) for Psychiatric Disorders Axis I [25].

The second visit (6 to 8 weeks after delivery) includes the following: assessments of depression with the Beck Depression Inventory (BDI) [26] the Edinburgh Perinatal Depression Scale EPDS [27], of maternal anxiety with the Scale Trait Anxiety Inventory (STAI) [28] of personality disorders using the screening of the International Personality Disorders Examination (IPDE) [29] and of maternal attachment patterns with the Adult Attachment Narratives (AAN) [30].

The third visit (6 months after delivery) includes assessments of mother-infant interaction during a meal with the Coding Interaction Behavior system (CIB) [31, 32], of the child’s temperament with a questionnaire on the 6-month-old infant’s temperament (QT6) [33, 34], of maternal depression (EPDS) [27] of child development using the Denver Developmental Screening Test [35] and of the relational retreat behavior of the child with the Alarm Distress Baby (ADBB) Scale [36] and the semi-structured interview for personality disorders (IPDE) [29].

The fourth visit (12 months after delivery) includes evaluations of maternal depression (BDI and EPDS), of maternal anxiety (STAI), of perceived social support (PSSQ), of interactions during a meal (CIB), of child development (DSST) and of the relational retreat behavior of the child (ADBB).

The fifth visit (18 months after delivery) includes evaluations of the infant’s pattern of attachment with the SSP (Strange Situation Procedure) [35] and of the infant’s development (DSST).

The sixth visit (20 months after birth) is a free assessment with the objective of thanking the parents for their participation and surveying them about the organization and design of this study.

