## Objectives

### Study hypothesis

We put forward the following hypothesis: an insecure attachment of the mother would participate or at least would increase the likeliness of pregnancy denial. These mothers would find it difficult (even impossible in some cases) to access the experiences of their infants, which are essential in the psychological reorganizations necessary during pregnancy to prepare the woman to accept her new functions as a mother.

Moreover, the absence or reduction of the duration of the usual 9-month period for psychological elaboration during the pregnancy calls into question its potential impact on the quality of mother-child interactions. Are there consequences on the infant’s development as well as on his pattern of attachment? We hypothesize that the attachment and the development of the infant to be born, as well as the quality of mother-infant interaction, are disturbed when the woman presents a denial of pregnancy. Specifically, we expect these consequences to be stronger with a longer duration of pregnancy denial.

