### Study objectives

The primary objective of this study is to examine the relationship between pregnancy denial and infant attachment patterns, early mother-infant interaction and early infant development.

The secondary objectives of this research are as follows:To explore among women with pregnancy denial the influence of the duration period between the pregnancy announcement and delivery on infant attachment pattern, early mother-infant interaction and early infant development;To study the factors associated with pregnancy denial, including the type of maternal attachment and the existence of a maternal personality disorder and/or a psychiatric condition.

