The infant’s development is evaluated with the Denver Developmental Screening Test [35]. The child level is assessed in different areas, such as gross motor skills, language, fine motor skills, and social contact.

Social contact is also evaluated on the Alarm Distress Baby Scale [36]. This scale includes 8 items concerning facial expression, eye contact, body activity, self-simulation gestures and finger activities, level of vocal expression, liveliness of a response to stimulation, ability to connect with someone else and attractiveness.

For the mothers: The representations of the adult’s attachment are studied with the Adult Attachment Narrative [30] through the analysis of 4 narratives (2 referring to relations among adults, and 2 in mother-child relations) built by the subject. The adult is asked to create a story using 12 words presented by the examiner (these words establishing the weft of the history). These narratives are blind-recorded and analyzed by trained professionals, and every narrative receives a note from 1 to 7 reflecting the secure base of the script in connection with the pattern of attachment of the subject. The average obtained on these 4 narratives estimates the security of the attachment of the subject and allows for the categorization into 2 groups: notes ≥ 3, insecure pattern of attachment; and notes > 3, secure patterns of attachment. The interview lasts approximately half an hour. The entire interview is transposed verbatim to allow for quotations.

The evaluation of personality disorders described in the ICD-10 is completed with the International Personality Disorders Examination (IPDE) [29]. This semi-structured diagnostic interview contains 67 items. The criteria of personality are grouped into six domains: work, personal, interpersonal relations, affects, apprehension of reality and control of impulses. The length of administration of the instrument varies between 60 and 90 minutes.

The main psychiatric disorders of the axis I of the ICD-10 are explored with the Mini International Neuropsychiatric Interview (MINI) [25]. This structured diagnostic maintenance tool contains 120 questions and is divided into 16 modules, each corresponding to a diagnosis category. The MINI was simultaneously developed in French and in English.

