### Statistical methods

Data will be described using means and standard deviations for quantitative variables and numbers and percentages for qualitative variable. Normal distributions will be checked.

To study factors associated with pregnancy denial, characteristics of women with pregnancy denial and characteristics of women without pregnancy denial will be compared with univariate analysis (using Student’s t, Wilcoxon, chi-square or Fisher’s exact tests, as appropriate) and multivariate analysis (logistic regression).

Factors associated with the attachment pattern of the child, divided into two categories (“secure” and “insecure”), will be studied by univariate (Student’s t, Wilcoxon, chi-square or Fisher’s exact tests, as appropriate) and multivariate analysis (logistic regression).

A *P*-value <0.05 will be considered statistically significant.

All analysis will be performed using SAS version 9.4 (SAS Inc., Cary, NC, USA).

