## Discussion

This study aims to examine the pathogenesis of pregnancy denial as well as its consequences on the attachment pattern of the child, the quality of early mother-infant interaction and infant development. We expect this study to more clearly define what pregnancy denial is and, thus, to improve the care of mother-infant dyads.

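### Maternal attachment and the direct psychiatric assessments all follow denial and its discovery, so the analysis of factors for denial cannot separate a contributor from a consequence

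*Protocol article*

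**What the plan says.** The Study hypothesis section of the protocol article gives an order of events: "an insecure attachment of the mother would participate or at least would increase the likeliness of pregnancy denial". The Discussion, and the Discussion paragraph of the Abstract, present the aim in the same causal terms: "This study aims to examine the pathogenesis of pregnancy denial". The Study objectives section is more modest: "To study the factors associated with pregnancy denial, including the type of maternal attachment", together with maternal personality disorder and psychiatric condition.

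Recruitment comes after the event: "Participation to the study will be proposed during hospitalization after delivery". Under Prospective visit calendar, the MINI is given at visit 1, in the week after delivery. Visit 2, at 6 to 8 weeks, includes IPDE screening "and of maternal attachment patterns with the Adult Attachment Narratives (AAN". The IPDE interview is at 6 months. Table 1 shows the AAN at visit 2 only. Visit 1 also draws the mother's psychiatric history from her charts.

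Under Measures, the AAN score is the average of four narratives, "2 referring to relations among adults, and 2 in mother-child relations", and is then cut into a secure and an insecure group.

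Under Statistical methods, "characteristics of women with pregnancy denial and characteristics of women without pregnancy denial will be compared with univariate analysis", followed by logistic regression. The section does not distinguish states that preceded denial from states recorded after it.

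**The concern.** A claim that attachment or psychiatric condition contributed to denial needs information on the mother's state before the denied pregnancy. The instruments record her state after she has learned of the pregnancy late or at birth and, for the AAN and IPDE, after weeks or months of caring for the infant. The article's own theory makes a later change plausible. The background section on consequences describes pregnancy as a psychological reorganization that hardly takes place in denial, and the hypothesis section expects the quality of mother-infant interaction to suffer. Half of the attachment score comes from stories about mother-child relations, which lie close to that domain.

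A significant odds ratio for insecure maternal attachment, or for a psychiatric diagnosis, could then reflect the aftermath of denial yet be read as support for the hypothesis. The Bias and the Strengths and limitations sections name drop-out as the threat to the results. Neither mentions the timing of measurement.

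**Working it through.** **1. Timing.** Denial and its discovery end at delivery at the latest. Against that point:

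| Factor | Measure | When |
|---|---|---|
| Maternal attachment | AAN | 6–8 weeks after delivery |
| Psychiatric condition | MINI | week after delivery |
| Personality disorder | IPDE screening / interview | 6–8 weeks / 6 months after delivery |
| Psychiatric condition | chart history | collected at visit 1; can refer to the time before pregnancy |

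Only the last row can reach back before the pregnancy, and the article does not say that this row is the variable used in the model.

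**2. Content.** Mother-child narratives make up 2/4 = 50% of the AAN average.

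**3. Illustration for attachment.** The plan has no figure of its own to reproduce here: its only power statement concerns the infant disorganization score. The inputs below are assumptions, except the 70 per group.

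Suppose there is no difference before pregnancy, and denial lowers only the two mother-child narratives, by *s* (in SD units of one narrative). Let ρ be the correlation between narratives.

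- Shift of the four-narrative mean = 2*s*/4 = *s*/2
- SD of the mean = √((1 + 3ρ)/4) = 0.689, 0.791, 0.880 for ρ = 0.3, 0.5, 0.7
- Standardised difference for *s* = 0.5: 0.25/SD = 0.363, 0.316, 0.284
- Two-sided 5% t-test, 70 per group (noncentral t): significant in 56.8%, 45.9%, 38.5% of studies
- For *s* = 0.3: 24.8%, 20.0%, 17.0%

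**4. The same shift on the two-category variable.** Take P(insecure) in controls as p₀ (assumed) and in cases as p₁ = Φ(Φ⁻¹(p₀) + d), where d is the standardised difference. Comparing two proportions with 70 per group (normal approximation) and *s* = 0.5:

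| ρ | p₀ = 20% | p₀ = 30% | p₀ = 50% |
|---|---|---|---|
| 0.3 | 35% | 38% | 39% |
| 0.5 | 27% | 30% | 31% |
| 0.7 | 23% | 25% | 26% |

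For *s* = 0.3 the range is about 11 to 17%.

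**5. Illustration for psychiatric condition.** Assume a prevalence before pregnancy of 15% in both groups, and new reactive disorder in a share *x* of otherwise unaffected cases. Then p₁ = 0.15 + 0.85*x* = 0.1925, 0.235, 0.2775 for *x* = 5%, 10%, 15%. The odds ratios against 0.15/0.85 are 1.35, 1.74 and 2.18 instead of 1. With 70 per group they would reach significance in about 10%, 25% and 45% of studies.

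**6. Reliability of a shorter score.** Spearman-Brown, kρ/(1 + (k − 1)ρ), at an assumed ρ = 0.5: four narratives 2.0/2.5 = 0.80; two narratives 1.0/1.5 = 0.67.

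**The case against.** The objective and the Statistical methods section already speak of factors associated with denial, and no rule declares the hypothesis supported by a significant odds ratio. Denial is recognised late by definition, so assessment after the event is built into recruitment on the maternity ward. The hypothesis section expects harm to the infant's attachment and to interaction; it does not say that denial changes the mother's own attachment representations. The AAN uses stories built from words supplied by the examiner, so it is not a report on her new infant. Any shift in the mother-child stories is therefore an assumption.

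Much of this stands. It limits the point to interpretation, to one sensitivity analysis and to the choice of the psychiatric variable. It does not remove the point: the article uses causal language in the hypothesis, Abstract and Discussion, and does not warn the reader about timing.

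Two stronger readings are tempting and are not supported:

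- A reader might infer that psychiatric condition is known only after delivery. Chart history is also collected.
- A reader might infer that the mood, anxiety and support scales are entered as predictors of denial. The Statistical methods section names no covariates, and the objective names only attachment type, personality disorder and psychiatric condition.

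**Conclusion.** The point holds for a secondary objective. Attachment, MINI and IPDE are all recorded after the denial and its discovery, so the planned comparison and regression cannot tell a contributor to denial from a consequence of it. The causal wording in the hypothesis, Abstract and Discussion goes beyond what these data can show. This conclusion rests on the visit schedule alone.

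The size is unknown. The rates of 39 to 57% and the odds ratios of 1.35 to 2.18 illustrate what could happen under assumed shifts, correlations and prevalences; they are not estimates for this study. The rates fall to about 23 to 39% for the two-category attachment variable that the plan defines. A reader might take any of these figures as the study's false-positive rate, but the document gives no AAN variance, correlation or prevalence from which such a rate could be derived. No sample-size figure is affected.

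**What to change.** - **Statistical methods, psychiatric factor:** in the model for denial, use chart psychiatric history from before the pregnancy. Report post-delivery MINI and IPDE results separately, as characteristics after delivery.
- **Statistical methods, attachment:** report the case-control comparison for the two adult-relation narratives alone beside the four-narrative score. Label it a sensitivity analysis that reduces but does not remove reverse causation. Both scores come from the same post-delivery visit, so their agreement cannot show that attachment came first and should not license a claim of contribution.
- **Abstract and Discussion:** replace the pathogenesis wording with factors associated with denial, as the objective already has it.
- **Strengths and limitations:** add that maternal attachment and the direct psychiatric and personality assessments were made after delivery.

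Selecting MINI or IPDE diagnoses by date of onset is not proposed, because the article does not say that onset dates are recorded.

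The cost is wording and one extra analysis of narratives that are already scored individually; no new data are needed. The two-narrative score is less reliable (0.67 against 0.80 under the assumed correlation of 0.5), chart history may be incomplete, and the claim becomes more modest.

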### Measures

For the infants: The attachment pattern of the infant is assessed with the Strange Situation Procedure [37, 38] A mother and an 18-month-old infant are under observation in a laboratory. The observer notes the child’s reactions during 8 episodes of 3 minutes involving the separations and reunions between the mother and the child, as well as the introduction of a stranger. The situation is videotaped. The coding system of interactive behaviors allows a categorization into 4 attachment patterns: “secure”, “anxious-avoidant insecure”, “anxious-resistant insecure” and “disorganized/disoriented insecure” (regrouped into two categories: “secure” and “insecure”). Richters and associates [39] developed a method to score attachment in a continuous way. Van IJzendoorn and Kroonenberg [23] adapted and validated the algorithm for use with Strange Situation interactive scales without scores for crying. The resulting algorithm yields a continuous score for attachment that is strongly associated with the insecure vs. secure attachment classifications. Higher security scores indicate a more secure attachment relationship. Continuous scores for disorganization were derived directly from coding the conventional 9-point scale for disorganization [40], with higher scores indicating more disorganized behavior.

The quality of early mother-infant interaction is assessed with the Coding Interactive Behavior (CIB) of Feldman [31, 32]. The CIB includes 42 items (21 concerning the mother, 16 concerning the child and 5 concerning the dyad). Each item is evaluated on a 5-point scale. During the first year, 6 dimensions are extracted from the CIB items: (i) parental sensitivity, (ii) parental intrusion, (iii) infant’s social engagement, (iv) infant’s negative emotionality/infant’s engagement, (v) dyadic reciprocity and (vi) dyad’s negative states. The scale consists of 2 segmentations of 15 minutes of interactions: one session of a game and one session of feeding. The 6-month-old infant’s temperament is assessed with the French version of the Infant Characteristics Questionnaire of Bates [33]. The QT6 is a self-questionnaire administered to the mothers with 26 questions about the “difficult” temperament of the infant. It was validated in France with 794 mothers of infants aged 6 to 9 months [34].

The infant’s development is evaluated with the Denver Developmental Screening Test [35]. The child level is assessed in different areas, such as gross motor skills, language, fine motor skills, and social contact.

Social contact is also evaluated on the Alarm Distress Baby Scale [36]. This scale includes 8 items concerning facial expression, eye contact, body activity, self-simulation gestures and finger activities, level of vocal expression, liveliness of a response to stimulation, ability to connect with someone else and attractiveness.

For the mothers: The representations of the adult’s attachment are studied with the Adult Attachment Narrative [30] through the analysis of 4 narratives (2 referring to relations among adults, and 2 in mother-child relations) built by the subject. The adult is asked to create a story using 12 words presented by the examiner (these words establishing the weft of the history). These narratives are blind-recorded and analyzed by trained professionals, and every narrative receives a note from 1 to 7 reflecting the secure base of the script in connection with the pattern of attachment of the subject. The average obtained on these 4 narratives estimates the security of the attachment of the subject and allows for the categorization into 2 groups: notes ≥ 3, insecure pattern of attachment; and notes > 3, secure patterns of attachment. The interview lasts approximately half an hour. The entire interview is transposed verbatim to allow for quotations.

The evaluation of personality disorders described in the ICD-10 is completed with the International Personality Disorders Examination (IPDE) [29]. This semi-structured diagnostic interview contains 67 items. The criteria of personality are grouped into six domains: work, personal, interpersonal relations, affects, apprehension of reality and control of impulses. The length of administration of the instrument varies between 60 and 90 minutes.

The main psychiatric disorders of the axis I of the ICD-10 are explored with the Mini International Neuropsychiatric Interview (MINI) [25]. This structured diagnostic maintenance tool contains 120 questions and is divided into 16 modules, each corresponding to a diagnosis category. The MINI was simultaneously developed in French and in English.

The mothers’ depressive feelings are evaluated with two scales. First, the Edinburgh Postnatal Depression Scale [27] a quick postnatal-specific self-questionnaire screening for postnatal depression, has been validated by a number of studies. Second, the Beck Depression Inventory [26] includes 21 items of symptoms and attitudes that describe a specific depressive behavior, with response options ranging from 0 to 3 by a series of 4 statements reflecting the degree of severity of the symptom.

The mothers’ anxious feelings are evaluated with Spielberger’s State-Trait Anxiety Inventory Form Y [28]. The inventory is intended to estimate, on the one hand, trait anxiety, and on the other hand, state anxiety, through 20 items that only focus on the psychological and not the somatic aspects of anxiety. The Y version was developed to eliminate items more bound to depression. The STAI is intended for self-administration, and every answer to an item of the questionnaire corresponds to a score from 1 to 4.

The availability of and satisfaction with the social support received are evaluated with the Perceived Social Support Questionnaire [24] a self-assessment scale that estimates the 4 main forms of social support, represented in 4 questions on the scale: the support of esteem, material or financial support, informative support, and emotional support. For each type of support, it assesses how many people dispense it, who these people are (family, friends, colleagues, professionals) and if the subject is satisfied with this support. Two scores are obtained for every subject: availability (number of people having participated in the support) and received satisfaction ("quality") of this support.

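### The maternal attachment cut-off in the Protocol article's Measures section cannot be applied as printed: the secure and insecure rules overlap above 3 and leave every mean below 3 unclassified

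*Protocol article*

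**What the plan says.** The Measures section of the Protocol article describes the Adult Attachment Narrative. Maternal attachment is studied "through the analysis of 4 narratives (2 referring to relations among adults, and 2 in mother-child relations) built by the subject". For the scoring, "every narrative receives a note from 1 to 7 reflecting the secure base of the script". The four scores are then combined: "The average obtained on these 4 narratives estimates the security of the attachment of the subject and allows for the categorization into 2 groups". The two groups are defined as "notes ≥ 3, insecure pattern of attachment; and notes > 3, secure patterns of attachment".

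The article does not restate or correct this cut-off anywhere else. The variable is used in three places:

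- **Study hypothesis.** Insecure attachment in the mother is put forward first, as something that contributes to denial or makes it more likely.
- **Study objectives.** The second of the two secondary objectives is "To study the factors associated with pregnancy denial, including the type of maternal attachment", together with personality disorder and psychiatric conditions.
- **Statistical methods.** Factors associated with denial are to be compared between cases and controls by univariate tests and logistic regression.

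**The concern.** A two-group classification has to give each mother exactly one label. The printed rule does not. Both inequalities point the same way from the same threshold, so the secure group lies wholly inside the insecure group, and nothing is assigned below the threshold.

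This is the only categorisation of maternal attachment that the article gives. As printed, the type of maternal attachment, which is the exposure in the first hypothesis, has no usable definition. An analyst has to repair the rule before using it. If the repair is not written down beforehand, the article leaves open which label a mother with a mean of exactly 3 receives.

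**Working it through.** The plan gives no figure to reproduce here. The check is on the logic of the rule, and alpha, power and sample size do not enter.

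**Inputs, all from Measures.** Four narratives; each scored from 1 to 7; the mean of the four is categorised; the mean estimates security, so higher is more secure; insecure if mean ≥ 3; secure if mean > 3.

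**Step 1: the inequalities alone.** Let m be a mother's mean.

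- m > 3: m ≥ 3 is true and m > 3 is true, so she is both insecure and secure.
- m = 3: m ≥ 3 is true and m > 3 is false, so she is insecure only.
- m < 3: both are false, so she has no category.

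This needs no assumption about whether scores are whole numbers.

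**Step 2: counting the possible means.** The article does not say that scores are whole numbers, so this step assumes it. The sum of four scores then runs from 4 to 28, which gives 28 − 4 + 1 = 25 possible means, from 1.00 to 7.00 in steps of 0.25.

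- Above 3: sums 13 to 28, which is 16 values (means 3.25 to 7.00).
- Exactly 3: sum 12, which is 1 value.
- Below 3: sums 4 to 11, which is 8 values (means 1.00 to 2.75).
- Check: 16 + 1 + 8 = 25.

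**Step 3: possible repairs, applied to the same 25 means.**

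| Rule | Insecure only | Secure only | Both | Neither |
|---|---|---|---|---|
| As printed (≥ 3 insecure, > 3 secure) | 1 | 0 | 16 | 8 |
| ≤ 3 insecure, > 3 secure | 9 | 16 | 0 | 0 |
| < 3 insecure, ≥ 3 secure | 8 | 17 | 0 | 0 |

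Both repairs classify every mean once. They differ only at a mean of exactly 3.00.

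**Step 4: which clause is wrong.** Each score reflects the secure base of the script, and the average estimates security. High means should therefore be secure. The secure clause (> 3) agrees with that and the insecure clause (≥ 3) contradicts it. Reversing the insecure inequality to ≤ 3 changes one symbol and makes the two clauses exact complements.

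The counts are of possible score values. They are not proportions of mothers, and the article gives no score distribution from which to estimate those.

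**The case against.** The strongest reply is that this is a one-symbol slip that any careful reader can repair. Much of that stands. The direction of the scale is stated in the same paragraph, the secure clause agrees with it, and the complement of that clause is ≤ 3. The only question left after that inference is where a mean of exactly 3 belongs. The raw scores are unaffected too: the Coding section has the narratives rated by trained raters blind to group status, so the split can be corrected at any time. A symbol misread in text extraction cannot be wholly excluded, although nothing in the text suggests one.

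The reply does not remove the point. The error is in the operational definition of a hypothesised exposure, and the article states a rule and states it wrongly. This is not a detail left to an analysis plan.

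A reader might infer three stronger things, and the document supports none of them.

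- **That the main result or the sample size is compromised.** The primary objective concerns infant attachment, mother-infant interaction and infant development. The infant secure/insecure split comes from the Strange Situation Procedure, and the sample size rests on the infant disorganization score. The maternal cut-off enters none of these.
- **That the association with denial will be reported in reverse.** If only the first clause were coded, with everyone else called secure, the labels would swap for every mean except exactly 3. An assumed odds ratio of 3 would then become about 1/3. That requires an analyst to ignore the second clause and the stated meaning of the scale. Anyone applying both clauses meets the contradiction at once. The odds ratio of 3 is an illustration and not a protocol figure.
- **That the two-group split should give way to the continuous mean.** A wrong inequality does not show that dichotomising is wrong, and the secondary objective asks about the type of attachment.

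**Conclusion.** The point holds as an error in a variable definition. As printed, means above 3 meet both rules, means below 3 meet neither, and only a mean of exactly 3 gets a single label. This follows from the inequalities alone. The count of 16, 8 and 1 out of 25 also assumes whole-number scores.

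The insecure inequality appears to be reversed, a conclusion that rests on the article's own statement that the average estimates security. The scoring source was not available to confirm it. The consequence is confined to the maternal attachment factor, in the first hypothesis, the secondary objective on factors associated with denial, and the planned univariate and logistic analyses of it. The intended direction can largely be recovered from the text, so the practical weight is moderate. The rule still needs correcting because it cannot be applied as it stands.

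**What to change.** In Measures, replace the cut-off with mutually exclusive and exhaustive rules on the mean of the four scores. The simplest is insecure if the mean is ≤ 3 and secure if the mean is > 3. Confirm the handling of a mean of exactly 3 against the instrument's scoring source, which the article cites, and record the rule before the case-control comparison of maternal attachment is run.

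The cost is one symbol and one check against the source. No new data, rescoring or change to the sample size is needed. The continuous 1 to 7 mean could be analysed alongside the two groups if the sponsor wishes, but this error does not require it.
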